## Abstract

**Background/Objectives**: There is a need for randomized clinical trials with higher quality, especially for older people at high risk of falls, with interventions that consider individual needs, comprehensiveness of care, and connection with primary health care. We designed a randomized controlled trial to examine the effects of a case management intervention combined with a physical exercise protocol on risk factors for falls, falls data, adherence, satisfaction, costs, and implementation in community-dwelling older adults with high risk of falls. **Methods**: A minimum of 60 community-dwelling older people with high falls risk will participate in the randomized controlled assessor-blinded trial (MAGIC—v. 2). The trial will be conducted in a regional health department of São Paulo state (Brazil), which includes 6 cities. Participants will be randomized to the Intervention Group (case management intervention based on all individual risk factors for falls identified by a multidimensional assessment, over 16 weeks, once a week, by telephone calls). Both groups will perform a physical exercise protocol based on falls prevention for 16 weeks (twice a week) in Health Units. The assessment will be performed at baseline, after 16 weeks of intervention, after 6-month follow-up, and after 12-month follow-up. Primary outcome measures include falls data and potentially modifiable risk factors for falls. **Discussion**: This study has the potential to facilitate the future implementation of the intervention based on case management with a focus on fall prevention in the health sectors. **Trial registration**: Brazilian Registry of Clinical Trials (ReBEC).

## 1. Introduction

Approximately 30% of community-dwelling older people suffer at least one fall yearly [1]. In addition to the high prevalence, falls in older people can lead to several serious consequences, such as fear of falling, functional decline, cognitive decline, social isolation, risk of depression, fracture, head injury, institutionalization, and death [2]. According to the Global Recommendation for the Prevention and Management of Falls in Older Adults [3], older adults at high risk of falls have a history of at least one fall in the last year and one or more of the following characteristics: (i) injurious fall, (ii) multiple falls (≥2 falls) in the last year, (iii) presence of frailty syndrome, (iv) inability to get up after a fall without help for at least one hour, and (v) fall accompanied by (suspected) transient loss of consciousness.

Falls constitute a global public health problem with great social impact. Falls prevention is essential, especially among older people with high risk of falls [3,4]. Older people in a more fragile situation and at high risk of falls benefit from individual interventions with a multifactorial approach. One of the multifactorial interventions for reducing falls risk is based on case management [3,5]. Case management intervention consists of identifying problems and conditions that can be changed to meet the identified needs of the older person and family. This care model can offer physical, psychological, and social assistance, which goes beyond traditional health care models [6].

Case management can be an intervention that develops and implements individualized and personalized plans to prevent future falls and reduce their risks and consequences [5,6,7]. In a systematic review, only 12 clinical trial studies involving case management based on falls prevention and reducing risk factors for falls in older people were found until 2023 [5]. There was limited evidence on falls rates and some risk factors for falls. Furthermore, adherence to recommendations varied widely between studies (25 to 88%) and no study assessed satisfaction with the intervention and other factors related to implementation. There is a need for higher-quality randomized clinical trials, especially for older people at high risk of falls, with interventions that consider individual needs, comprehensiveness of care, and connection with primary health care [5].

The Multidisciplinary and Assistance Program of Falls Management in Faller Older People (MAGIC, v. 1) [8] ended in 2024. Despite the positive results of the previous protocol, the present protocol (MAGIC, v. 2) represents an advance in certain respects, including (i) proximity to the public network in order to favor the implementation of the intervention based on case management focused on preventing falls [3] in the context of health care, especially primary care; (ii) target audience of older people with high falls risk, according to the last Worldwide Guideline [3]; (iii) assessments at home instead of remote format; (iv) possibility of investigating minimal clinically relevant differences for the tests used in this population [9,10]; (iv) adding all potentially modifiable risk factors for falls to the case management intervention, since the probability of falls occurring increases as risk factors accumulate [3]; (v) the possibility of using technologies in the intervention; (vi) understanding adherence and satisfaction in a long term; and (vii) having a Control Group submitted to a physical exercise program based on falls prevention in the primary care.

We expect that the case management program combined with physical exercise will show additional benefits compared to physical exercise alone in community-dwelling older people with a high risk of falls. The purpose of this protocol is to evaluate the effectiveness of a case management intervention combined with physical exercise compared to physical exercise alone in reducing risk factors for falls, preventing falls, improving adherence and satisfaction, and assessing costs and implementation feasibility in older people at high risk of falls.

## 2. Materials and Methods

### 2.1. Trial Design

The MAGIC (v. 2) trial is a randomized, controlled, assessor-blinded, single-center (one main research center with collaborators from other centers, with an expectation to cover at least 8 different health territories) superiority trial with two parallel groups. The randomization will be performed as block randomization (random sizes) with a 1:1 allocation (Figure 1).

### 2.2. Study Setting

This research was approved by the Research Ethics Committee of the Federal University of São Carlos (CAAE: 86710225.5.0000.550) on 28 April 2025, and was registered and approved in the Brazilian Registry of Clinical Trials (ReBEC) on 30 June 2025 (code: RBR-8srwcqg). The health system of São Paulo state (Brazil) is divided into 17 regional health departments (DRSs). The DRSs are responsible for coordinating the activities of the State Health Department at the regional level and promoting intersectoral collaboration with municipalities and civil society organizations. This trial will be conducted in the Araraquara DRS (Coração region), which includes six cities (Descalvado, Dourado, Ibaté, Porto Ferreira, Ribeirão Bonito, and São Carlos).

The responsibilities of the Araraquara DRS include the coordination of health actions to ensure the implementation of policies under the Unified Health System (SUS); regulation of access to consultations, exams, and hospital procedures at the primary, secondary, and tertiary care levels, ensuring patients are directed to appropriate services within the region; promotion of formative spaces for the integration and training of professionals to address local and regional demands; and management of human and financial resources in accordance with local needs.

The region was chosen for operational purposes, taking into account that the research center is situated in São Carlos city, which is located in the center and is the reference city of this DRS. According to the latest census conducted in 2022 by the Brazilian Institute of Geography and Statistics (IBGE), the region comprising these six municipalities has a population of 390,525 inhabitants, of which 64,148 (16.54%) are older individuals [11].

### 2.3. Recruitment and Participants

Screening will continue until the target population is achieved. The subjects will be recruited by telephone contact during business hours among eligible individuals and individuals treated at primary to tertiary health units, social and educational services, and from the research group’s database and some community groups. In addition, there will be dissemination through pamphlets, posters, radio and television channels, and social networks, with the assistance of the UFSCar’s communication team. The enrollment period will extend over 9 months.

The volunteers will provide written, informed consent before any study procedures occur. People eligible for the trial will be aged ≥60 years old, resident in the Araraquara DRS (Coração region), non-institutionalized, with a history of at least one fall in the last year, and possibility of contact by telephone. Inclusion criteria will be a level of consciousness that allows the volunteer to be an active subject in the intervention; high falls risk according to the Worldwide Guideline for falls prevention and management for older adults [3], i.e., older adults with a history of at least 1 fall in the last year and one or more of the following characteristics: (i) injurious fall, (ii) multiple falls (≥2 falls) in the last year, (iii) presence of frailty syndrome, (iv) inability to get up after a fall without help for at least one hour, and (v) fall accompanied by (suspected) transient loss of consciousness; ability to walk alone with or without a walking aid; and willingness to participate in the proposed assessments and interventions.

Exclusion criteria will be as follows: a severe and uncorrected hearing and visual impairment that hinders communication during the intervention; neurological diseases that rapidly modify falls risk, including multiple sclerosis, diagnosis of moderate to advanced dementia, epilepsy, and traumatic brain injury, or taking associated medications; and contraindication to physical exercise (acute infectious disease, dissecting aortic aneurysm, severe aortic stenosis, congestive heart failure/unstable angina, acute myocardial infarction, acute myocarditis, acute pulmonary or systemic embolism, thrombophlebitis, ventricular tachycardia, and other dangerous arrhythmias) (Figure 2).

The sample size was calculated based on the primary outcome measures (potentially modifiable risk factors for falls, especially motor risk factors). The sample size was calculated using the statistical program G*Power 3.1, assuming (1) the purpose of identifying the effectiveness of risk factors after 16 weeks of intervention; (2) the test used (two-way ANOVA, considering group and time effects, with Bonferroni test to control type I error due to multiple primary outcomes); (3) the main measure; (4) type I error at 5%; (5) statistical power at 80%; and (6) an effect size of 0.25, a minimum of 28 people should constitute the total sample. Furthermore, to verify the sociodemographic and clinical factors that influence adherence and satisfaction, the rule of at least 10 cases of the outcome (success or failure, depending on which is rarer) was used for each independent variable used in the logistic/linear regression model [12]. Thus, considering an adherence of 80% based on a previous study by the research group [9] and the use of univariate regression analyses, a minimum of 50 people should constitute the total sample. With the chance of losing 20% of participants, a sample of 60 people in total is estimated.

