To verify the effectiveness of the interventions, the chi-square association test will be used for categorical variables. About the use of fNIRS, a pilot study was conducted before data collection, and the fNIRS signal demonstrated good quality across the targeted channels and participants, with minimal signal loss or saturation. This assured us the feasibility and reliability of the measurements. Regarding the data workflow, motion artifact control, and ROI selection, at this stage, the specific fNIRS data analysis is still ongoing, and a preregistered analysis plan has not yet been developed. We intend to finish this step until the end of 2025. Using the fNIRS, the digitizer data will be entered into the NIRS-SPM software package (v. 4), implemented in MATLAB 2017 (Natick, MA, USA). The fNIRS data will be preprocessed using custom MATLAB algorithms [51]. For quantitative variables, the two-way ANOVA test will be used to verify the interaction between groups and evaluations, with Bonferroni test to control type I error due to multiple primary outcomes. If an interaction is identified, simple main effects analyses will be performed, with adjustments for multiple comparisons (Bonferroni). To verify the proportion of individuals who did not suffer any fall episode during the 12-month follow-up (“proportion of people who did not have the first fall” and “proportion of people who did not have the second fall”), the Kaplan–Meier analysis will be used.

To verify adherence and satisfaction with interventions and sociodemographic and clinical factors that influence them, descriptive analyses of quantitative and qualitative data will be used, using the MAXQDA2022 software for coding and categorization. The excerpts of the responses will be separated into segments containing the ID of each volunteer and their corresponding code. After coding, the segments obtained will be organized using Bardin’s content analysis [52]. Furthermore, simple linear regression analysis will be used to verify possible influences of adherence (frequency) and satisfaction (score). Also, descriptive analyses and the chi-square association test will be used.

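### The 28-person, 80%-power figure is stated at an undivided 5% alpha although the plan applies Bonferroni across several primary outcomes; the power at the planned 60 is therefore not shown

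*Protocol article*

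**What the plan says.** Section 2.3 sets out the calculation: "The sample size was calculated based on the primary outcome measures (potentially modifiable risk factors for falls, especially motor risk factors"). Its stated purpose is the effect after 16 weeks of intervention. The listed assumptions are a two-way ANOVA (group by time) "with Bonferroni test to control type I error due to multiple primary outcomes); (3) the main measure; (4) type I error at 5" (per cent), then "5) statistical power at 80" (per cent) and "an effect size of 0.25, a minimum of 28 people should constitute the total sample". The main measure is listed but not named.

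A separate events-per-variable rule for the adherence regression gives 50. Allowing for 20% loss, the paragraph arrives at 60 in total.

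Section 2.9 commits the analysis to the same rule: the group-by-visit interaction of each quantitative measure is tested "with Bonferroni test to control type I error due to multiple primary outcomes". Section 2.6 makes falls data and the potentially modifiable risk factors primary and refers to Table 1, which has 16 risk-factor rows, most with several instruments.

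**The concern.** One sentence announces a Bonferroni correction across several primary outcomes and then enters the full 5% as the type I error. If each outcome is tested at 0.05/K, a sample sized at 0.05 has less than the stated power for each of them. The paragraph gives no K, so a reader cannot tell how much less.

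The effect size adds to the difficulty. A value of 0.25 looks like a conventional moderate effect, but in a group-by-time interaction it corresponds to a much larger difference between arms. This is the protocol's only power statement for its primary outcomes. If it cannot be relied on, a null result could be taken as evidence that case management adds nothing to exercise, when the trial's sensitivity was never properly stated.

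**Working it through.** **Inputs from the documents.** Two arms, 1:1; effect size 0.25, read as Cohen's f because the tool is G*Power with an ANOVA; alpha 0.05; power 80%; 28 in total; 60 enrolled with 20% loss, so 60 × 0.8 = 48 completers.

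**Inputs assumed, because they are not stated.** Number of visits m (2, 3 or 4; the 16-week purpose suggests 2, the full schedule has 4), within-person correlation r, sphericity, and the number of primary outcomes K. For K I use 2, 5, 6 (roughly the measures in Table 1's strength, mobility, gait and balance row), 16 (Table 1 rows) and 45 (a rough count of all the measures in Table 1).

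**Formula.** Group-by-time interaction, noncentral F: λ = N·m·f²/(1 − r), df1 = m − 1, df2 = (N − 2)(m − 1), tested at 0.05/K.

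**Reproducing 28 at K = 1.**

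- m = 3, r = 0.5: λ = 28 × 3 × 0.0625/0.5 = 10.5; power 0.81.
- m = 2, r = 0.6: λ = 28 × 2 × 0.0625/0.4 = 8.75; power 0.81.
- m = 4, r = 0.4: λ = 28 × 4 × 0.0625/0.6 = 11.67; power 0.81.

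In each setting 28 is the smallest even total that reaches 80%. A group main effect at r = 0.5 would need 82 to 98 instead, so the interaction is the reading that fits. Two visits with r = 0.5 need 34 even without correction.

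**Applying Bonferroni at f = 0.25.** Middle columns: range over the three settings that reproduce 28. Last column: two visits with r = 0.5, a setting that does not reproduce 28.

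| K | Power at 28 | Power at 48 | Power at 48 (m = 2, r = 0.5) |
|---|---|---|---|
| 1 | 0.81 | 0.97 | 0.92 |
| 2 | 0.72 | 0.94–0.95 | 0.87 |
| 5 | 0.58–0.59 | 0.88–0.90 | 0.78 |
| 6 | 0.55–0.57 | 0.86–0.89 | 0.76 |
| 16 | 0.40–0.44 | 0.77–0.81 | 0.64 |
| 45 | 0.28–0.32 | 0.65–0.72 | 0.50 |

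The total needed for 80% power at K = 16 is 48 to 52 in the three settings, and 64 with two visits and r = 0.5.

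**What f = 0.25 means.** With two arms and two visits, a between-arm difference in change of δ SD gives interaction cell effects of ±δ/4, so f = δ/4 and δ = 4 × 0.25 = 1.0 SD.

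**What 48 completers can detect in the planned ANOVA.** With two visits the interaction test is a t-test on change scores. The SD of change is √(2(1 − r)): 1.0 at r = 0.5 and 0.775 at r = 0.7. With 24 per arm the standard error is that SD × √(2/24) = SD × 0.289. For 80% power at two-sided 5% the multiplier is about 2.86 (46 df). The detectable difference is 2.86 × 0.289 = 0.83 SD at r = 0.5, and 0.83 × 0.775 = 0.64 SD at r = 0.7. A baseline-adjusted comparison would multiply these by √((1 + r)/2), giving 0.72 and 0.59 SD, but section 2.9 does not plan that analysis.

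**The case against.** The strongest reply is that 28 is only a floor. The same paragraph replaces it with 50 and then 60, and at 48 completers the assumed effect keeps at least 80% power up to K = 16 (m = 3, r = 0.5), K = 11 (m = 2, r = 0.6) or K = 18 (m = 4, r = 0.4). Even two visits with r = 0.5 hold 80% up to K = 4. This stands. A reader might infer that the trial as planned lacks 80% power for its primary outcomes; the documents do not support that, because they fix neither K, m nor r.

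The size of K is also open to argument. Section 2.3 stresses motor risk factors, and section 2.9 attaches Bonferroni to the ANOVA for quantitative variables, while categorical ones go to chi-square. Several Table 1 entries are categorical, so 45 probably overstates the ANOVA family. This stands too, and 45 should be read as an upper illustration.

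Arithmetic alone does not prove that alpha was left undivided: m = 4, r = 0.5, K = 2 and m = 2, r = 0.8, K = 16 also give 28. But the text states 5% and gives no divisor, so the statement as printed still does not match the planned test.

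Finally, a reader might take the 1.0 SD effect as proof that the power is not delivered, or that only a very large benefit could be seen. Neither follows. Power is conditional on the assumed effect, the documents give no smaller target, and 48 completers detect about 0.64 to 0.83 SD at an undivided 5%. Leaving m and r out of a journal article is ordinary condensation and is not itself the defect.

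**Conclusion.** The point holds in a limited form. The stated alpha, multiplicity rule, sample size and power do not fit together: in the settings that reproduce 28 at the stated 5%, any Bonferroni division with K of 2 or more takes power at 28 below 80%, to 0.40–0.44 if the 16 Table 1 rows are the family. At the planned 60, with about 48 completers, the problem is that adequate power is not demonstrated, not that it is shown to be absent. It is adequate for a family of about six measures in the settings that give 28, borderline at 16, and short with many more measures or with two visits and r = 0.5 once K reaches 5. All of this assumes f = 0.25, sphericity and the interaction reading. On that reading the assumed effect with two visits is a 1.0 SD difference in change. That is large for case management added to exercise that both arms receive, and it should be visible, but it is a matter of justification and not a calculation error.

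**What to change.** Reword the sample-size paragraph in section 2.3:

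1. Either name one primary measure at 16 weeks, tested at two-sided 5%, or keep several primaries, state K, and redo the calculation at 0.05/K. Align sections 2.6 and 2.9 with the choice.
2. Replace the claim of 28 at 80% power with the power or detectable difference at 48 completers for the planned group-by-time ANOVA. State the number of visits, r, and the effect in SD units with its basis. With two visits and an undivided 5%, the detectable difference is about 0.83 SD (r = 0.5) or 0.64 SD (r = 0.7).
3. Quote 0.72 or 0.59 SD only if the analysis is changed to a baseline-adjusted comparison.

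The cost is a rewritten paragraph and no extra patients, since 60 is set by the regression rule. The downside is that the stated sensitivity will look less favourable than the present text.

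### The 20% loss allowance is added to 50 (50 × 1.2 = 60) instead of being divided out, so 60 enrolled leaves 48 expected, marginally below the minimum of 50 for the secondary regressions

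*Protocol article*

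**What the plan says.** Section 2.3 (Recruitment and Participants) of the protocol article derives the sample size in three steps.

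- **Primary outcomes.** A G*Power calculation for a two-way ANOVA on risk factors at 16 weeks gives "an effect size of 0.25, a minimum of 28 people should constitute the total sample".
- **Adherence and satisfaction regressions.** The article applies a cases-per-variable rule: "the rule of at least 10 cases of the outcome (success or failure, depending on which is rarer) was used for each independent variable". It does so "considering an adherence of 80% based on a previous study by the research group" and with "the use of univariate regression analyses", and concludes that "a minimum of 50 people should constitute the total sample".
- **Loss.** The last sentence reads: "With the chance of losing 20% of participants, a sample of 60 people in total is estimated".

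The abstract repeats the result as a floor: "A minimum of 60 community-dwelling older people with high falls risk will participate". The article gives no other loss rate and no larger target.

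**The concern.** The last step allows explicitly for loss, so the 50 is meant as the number left after loss, and the 20% is worded as a share of participants. On that reading the three figures 50, 20% and 60 cannot all be true, because 60 less 20% is below 50.

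The 60 is the trial's headline size and rests on this step alone. What is at stake is whether the stated size delivers the number given to justify it. The number in question belongs to the secondary regressions on adherence and satisfaction, not to the primary comparison.

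**Working it through.** **Inputs, all from section 2.3**
- Rule: at least 10 cases of the rarer outcome per independent variable
- Assumed adherence: 80%, so the rarer outcome (non-adherence) is 20%
- Independent variables per model: 1 (univariate)
- Loss: 20% of participants
- Stated minima: 50 (regressions) and 28 (ANOVA)
- Stated total: 60

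**1. Reproduce the 50.** Cases needed / proportion with the rarer outcome = 10 / 0.20 = 50. This agrees with the article.

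**2. Reproduce the 60.**
- From 50, adding 20%: 50 × (1 + 0.20) = 60. Exact match.
- From 50, dividing by the retained share: 50 / (1 − 0.20) = 62.5, so 63. No match.
- From 28: 28 × 1.20 = 33.6, so 34; or 28 / 0.80 = 35. No match.

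The 60 therefore comes from the 50, with the loss taken as 20% of the retained number instead of 20% of the enrolled number.

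**3. Apply the stated loss to 60.** 60 × (1 − 0.20) = 48 expected to remain, and 50 − 48 = 2 short.

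**4. Loss that 60 can absorb.** (60 − 50) / 60 = 10/60 = 16.7%.

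**5. Number that meets both 50 and 20%.** 50 / 0.80 = 62.5, so 63, or 64 for equal arms under 1:1 allocation. Expected to remain: 63 × 0.80 = 50.4, or 64 × 0.80 = 51.2.

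**6. Effect on the 10-case rule.** If lost participants contribute no adherence value, the expected number of non-adherent cases is 48 × 0.20 = 9.6 against 10. If adherence is known for all 60, it is 60 × 0.20 = 12.

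**7. Chance of keeping at least 50.** This adds an assumption that the article does not make: each person is lost independently with probability 0.20. The binomial probability that at least 50 remain is:

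| Enrolled | P(at least 50 remain) |
|---|---|
| 60 | 0.32 |
| 63 | 0.62 |
| 64 | 0.71 |

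Even the correct inflation secures 50 only on average. Likewise, the chance of at least 10 non-adherent cases is 0.50 with 48 people and 0.56 with 50, so the practical difference is modest.

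**8. Primary minimum.** 48 − 28 = 20 above the stated ANOVA minimum. The 28 is taken as stated here and was not needed for this check.

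**The case against.** The arithmetic is hard to dispute, so the case on the other side concerns its consequence.

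- **The primary sizing is not touched.** This stands. The stated minimum of 28 is met with 48. A reader might infer from the shortfall that the trial is too small for its primary comparison, but the article's figures do not support that inference.
- **The 10-case rule need not fail.** This largely stands. Section 2.7 measures adherence by weekly frequency of the interventions, which may be known for people who later leave, and someone who stops attending early would tend to count as non-adherent. Section 2.9 plans simple linear regression of adherence frequency and satisfaction score, to which a count of rarer cases does not apply. Satisfaction does need the 16-week questionnaire, but it is a score and has no rarer outcome. It would therefore be too strong to say that the rule is broken.
- **The time point of the 20% is not given.** This stands as a caveat. Satisfaction and adherence to the interventions are assessed at 16 weeks, while follow-up runs to 12 months. If the 20% refers to 12 months, fewer may be lost by 16 weeks.
- **The abstract calls 60 a minimum.** More people may be enrolled, but this does not repair the step. Section 2.3 gives 60 as the total that already includes the loss, and that floor leaves 48.
- **Multiple imputation is planned for missing data (section 2.9).** It may help the analysis, but it does not make the stated inflation correct.

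**Conclusion.** The loss allowance is wrong as written. The article inflates 50 to 60 by adding 20%, and at a 20% loss of those enrolled 60 leaves 48 expected, not 50. The figure consistent with the article's own inputs is 63, or 64 for equal arms.

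The size of the error is 2 expected completers, or 3 to 4 enrolments. It affects the minimum for the secondary adherence and satisfaction regressions only. At most it means about 9.6 instead of 10 expected non-adherent cases, a marginal shortfall on a rule of thumb, and only if those lost contribute no adherence value.

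The conclusion assumes that the 20% is a share of enrolled participants, as the sentence is worded, and that the 50 is required after loss, as the act of inflating it implies. It neither confirms nor questions the 28.

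**What to change.** Correct the last sentence of the sample size paragraph in section 2.3 so that 50, 20% and 60 agree. There are three ways to do this.

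1. Keep 60 and 20%, and state that about 48 are expected to remain, marginally below the 50 sought for the secondary regressions.
2. Keep 60, and state that it retains 50 only if loss does not exceed 10 of 60 (16.7%). This should be worded as the limit that 60 can absorb, since nothing in the article supports it as the expected loss.
3. Keep both 50 and 20%, and set the total at 63 (64 for 1:1).

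The first two cost one sentence and no extra participants, and the abstract can stay as it is. The third costs 3 to 4 more participants and a matching change in the abstract.
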